### Secondary hypotheses

- Patient satisfaction >6 points (on a scale of 1-10) is not significantly different between both groups
- Outpatient recovery after standard bariatric surgery with Healthdot monitoring is feasible based on evaluating recruitment rate (>60% of patients), adherence to protocol (>75% of patients), and the amount of missing data (<10%).
- False-positive notifications from the Healthdot system are lower than 10% of notifications per patient.
- Missed events (false negatives) i.e. there was no notification from the Healthdot system when the patient needed to go to the hospital, are lower than 5% of all notifications.
- Missed minor events occur less than five times per patient. Missed minor events are defined as when there was no notification from the Healthdot system and the patient contacted the hospital, but there was no need for the patient to visit the hospital.
- The outcome of patients who choose HD versus patients who were randomized to HD on a combined outcome measure as defined for the primary endpoint are the same.
- The number of adverse events is not significantly different in both groups.

|                                                                                                                    |              |                        |                  |                    |
|--------------------------------------------------------------------------------------------------------------------|--------------|------------------------|------------------|--------------------|
| Title: Clinical Investigation Plan                                                                                 |              | Author: [name] |                  | Philips restricted |
| DocID: ICBE-2-36455                                                                                                | Version: 3.0 | Date: 2020-DEC-08      | Status: Approved | Page: 21 of 44     |
| This document is based on Philips Research Template: Clinical Investigation Plan, ID: QR-TEM-57, Date: 2019-Mar-21 |              |                        |                  |                    |

- The amount of pain medication during day of surgery until evening in both groups is not significantly different.
- Clinical decisions made on basis of remote monitoring with the Healthdot system do not change in more than 5% of cases when information from a telephone consultation is also included in the decision making process.

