- Patient and health professional satisfaction (on a scale from 1-10) for outpatient recovery after standard bariatric surgery with the Healthdot are equal or higher than for current treatment.
- The costs involved with outpatient recovery after standard bariatric surgery supported by Healthdot is less than the cost involved with the current recovery path, in the period up to 7 days after surgery.
- The usability of the visualization of Healthdot data on the Guardian dashboard is scored good (at least 4 out of 5).

These hypotheses will be accepted or rejected based on the outcome of this clinical investigation.

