### Claims and intended performance

In this investigation it will be tested if the Healthdot is suitable as a tool for out of hospital monitoring enabling a change in standard of care workflow for patients after surgery. Depending on the outcome claims may be derived from the primary and secondary hypothesis.

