## Statistical design

This study is primarily designed to test for non-inferiority of outpatient recovery compared to regular treatment for bariatric surgery. The outcome measure that we will use for the analysis is a combined measure, based on the following:

- Mortality
- Severe postoperative complications (Clavien-Dindo IIIb or higher)
- Readmission (at least one night in hospital)
- Mild complications (Clavien-Dindo II and IIIa)
- Prolonged length of stay (3 days or more in hospital)

within 30 days after primary surgery.

We choose to use this combined outcome measure since it is in line with other surgical studies [5] making it comparable to literature.

I current practice at Catharina Hospital, Eindhoven, 95% of all bariatric surgery patients do not have any of these events which is considered the textbook outcome here.

We set the following null and alternative hypotheses for proving non-inferiority:

$H_0: p_{\text{regular}} - p_{\text{outpatient}} \geq \Delta$

$H_1: p_{\text{regular}} - p_{\text{outpatient}} < \Delta$

Where  $p_{\text{regular}}$  is the textbook outcome proportion in the regular treatment group, and  $p_{\text{outpatient}}$  is the textbook outcome proportion in the outpatient recovery group. We will use a non-inferiority margin ( $\Delta$ ) of 7%, which is deemed clinically significant by the Principal Investigator. This is also justified by a previous study where the average textbook outcome across bariatric surgery patients in the Netherlands was 88,7% [5] which helps to derive a non-inferiority margin of around 7% to the one seen at Catharina Hospital. We will use an uncorrected chi-squared statistic. Based on the sample size calculation done below an p value of 0.05 will be considered statistically significant. For the interim analysis an alpha correction for multiple testings is applied and a p value of 0.025 will be considered statistically significant.

The secondary endpoints will be analysed statistically in analogy to the primary endpoint by uncorrected chi-squared statistic where deemed appropriate.

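### Three secondary hypotheses are met by a non-significant difference and a fourth asserts sameness, none with a margin, so moderate deficits can be accepted as equality

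*Protocol*

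**What the plan says.** Section 5 of the protocol, under Secondary hypotheses, words three comparisons of the outpatient and regular groups as an absence of statistical significance:

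- Satisfaction: "Patient satisfaction >6 points (on a scale of 1-10) is not significantly different between both groups".
- Adverse events: "The number of adverse events is not significantly different in both groups".
- Pain medication: "The amount of pain medication during day of surgery until evening in both groups is not significantly different".

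A fourth hypothesis compares patients who chose Healthdot with those randomised to it and says that their outcomes "on a combined outcome measure as defined for the primary endpoint are the same".

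The list closes with a decision rule: "These hypotheses will be accepted or rejected based on the outcome of this clinical investigation". The next subsection, Claims and intended performance, adds: "Depending on the outcome claims may be derived from the primary and secondary hypothesis".

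Section 7, Statistical design, says of the analysis: "The secondary endpoints will be analysed statistically in analogy to the primary endpoint by uncorrected chi-squared statistic where deemed appropriate". The same section sets the only non-inferiority margin in the protocol, 7 percentage points on the textbook-outcome proportion. The Sample size subsection powers that comparison alone.

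**The concern.** A non-significant test shows that the data did not exclude zero difference. It does not show that the difference is small. When a hypothesis itself says that there is no significant difference, and is to be accepted or rejected, non-significance is the criterion for success. The incentive then runs the wrong way: fewer patients, more missing data or noisier measurement all make acceptance more likely.

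The protocol handles this properly for its primary endpoint, with a margin, a null hypothesis of inferiority and a sample size. The four secondary hypotheses have none of these. At stake are statements that same-day discharge does not change adverse events, satisfaction or early pain-medication use, and that choosers and randomised patients fare alike. Section 3 gives the purpose of the trial as earlier discharge without additional risk to the patient, so a statement of no difference in adverse events is one that readers would rely on.

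**Working it through.** **The protocol's own figure.** The primary sample size reproduces as a one-sided non-inferiority calculation: n = (1.645 + 0.8416)² × 2 × 0.96 × 0.04 / 0.07² = 96.9, so 97 per group, which the protocol rounds to 100. It reproduces with alpha 0.05 one-sided; one-sided 0.025 would give 124. Section 7 does not state the sidedness of its 0.05 threshold, so both versions are shown below.

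**Inputs from the protocol.** 100 per group; alpha 0.05; uncorrected chi-squared where deemed appropriate; 95% of current patients free of any composite event, which gives a 5% reference rate; primary margin 7 points; 10% expected drop-out, replaced only in the first two days; missing measurements not imputed.

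**Assumptions.** The protocol states no adverse-event rate, no satisfaction rate, no spread for pain medication, and no expected split between choosers and randomised patients. All rates below are scenarios. Adverse events are treated as the share of patients with at least one event. The 5% reference is borrowed from the composite, although the protocol defines an adverse event more broadly, so higher rates are shown too.

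**Binary outcomes.** Let x_R of n_R patients in the regular group and x_O of n_O in the outpatient group have the event, with pooled proportion p̄ = (x_R + x_O)/(n_R + n_O). The uncorrected chi-squared statistic is z², where z = (x_O/n_O − x_R/n_R) / √[p̄(1 − p̄)(1/n_R + 1/n_O)]. The chance of a non-significant result is the sum of the two binomial probabilities over all outcomes with |z| ≤ 1.96 (two-sided), or z ≤ 1.645 (one-sided, towards harm).

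| True rates, 100 per group | Two-sided | One-sided |
|---|---|---|
| 5% vs 10% | 73% | 61% |
| 5% vs 12% (deficit equal to the primary margin) | 56% | 43% |
| 10% vs 20% (same as satisfaction 90% vs 80%) | 48% | 36% |
| 5% vs 15% | 32% | 21% |
| 5% vs 20% | 8% | 4% |

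With 90 per group, two-sided, 5% vs 12% rises from 56% to 60%, and 10% vs 20% from 48% to 53%. Losing data makes acceptance easier.

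**One observed result.** Take 5/100 versus 12/100. Then p̄ = 0.085 and z² = 0.07² / (0.085 × 0.915 × 0.02) = 3.15, so p = 0.076. The standard error of the difference is √(0.05 × 0.95/100 + 0.12 × 0.88/100) = 0.0391, and the 95% interval is 7 ± 1.96 × 3.91 points, or −0.7 to +14.7. Two-sided, the hypothesis would be accepted while the upper limit is about twice the primary margin. One-sided, z = 1.77 exceeds 1.645 and this result would be significant. At 11/100 it would not be: z = 0.06 / √(0.08 × 0.92 × 0.02) = 1.56.

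**Pain medication.** For a true standardised difference d, the two-sided chance of non-significance is about Φ(1.96 − d√(100/2)). This gives 71%, 44%, 19% and 6% for d = 0.2, 0.3, 0.4 and 0.5.

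**Chosen versus randomised Healthdot.** Only patients without a preference are randomised, so the randomised subset has no planned size. Assume 5% versus 15% failing the composite, split 100 patients between 60:40 and 90:10, and take non-significance as the test of sameness. The result is non-significant in 57% to 68% of trials two-sided, and 43% to 61% one-sided.

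**The case against.** The strongest reply is that little depends on these hypotheses. Pass/fail rests on the primary endpoint alone, which has a margin and already counts death, Clavien-Dindo grade II or higher complications, readmission and prolonged stay. Many clinically important adverse events are therefore tested properly. The secondary objectives are worded as assessing, comparing and evaluating. The protocol says only that claims may follow, and the executive summary records that no list of claims has been developed. This limits the consequence. It does not remove the rule, because the accept-or-reject sentence and the claims sentence both stand.

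The analogy with the primary endpoint in Section 7 might be read as non-inferiority testing for the secondary endpoints too. No secondary margin exists, and the hypotheses say otherwise, so that reading does not rescue them. Satisfaction has a further hypothesis of equal or higher scores, also without a margin.

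Three stronger readings are tempting and are not supported.

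- A reader might infer that the sameness of choosers and randomised patients is meant to justify pooling them. The protocol nowhere says so. Section 6.1 says only that preference is recorded so that it can enter the analysis.
- A reader might infer that chi-squared is prescribed for adverse-event counts and medication amounts. Section 7 limits it to where it is deemed appropriate, and the test for each endpoint may be left to a statistical analysis plan.
- A reader might infer that even gross harm would pass. At 5% versus 20% it would be missed in only 8% of trials.

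**Conclusion.** The concern holds for the stated acceptance rule. For satisfaction, adverse events and pain medication, the wording makes non-significance the success criterion. For chosen versus randomised Healthdot, sameness is asserted with no criterion for showing it, and a non-significant test would be the natural but inadequate substitute. This is a wrong rule fixed in the protocol, not a detail left open for later.

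The problem lies with moderate deficits: about a doubling of the event rate, or a difference near 7 points. In the two-group scenarios of that kind, equality would be accepted in 48% to 73% of trials two-sided and 36% to 61% one-sided. These figures rest on assumed rates with 100 analysed per group; the defect remains under either sidedness. The primary non-inferiority hypothesis and the pass/fail criterion are not affected.

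**What to change.** In Section 5 (Secondary hypotheses, and Claims and intended performance) and Section 7 (Statistical design):

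- Replace the non-significance and sameness wording with estimation of the difference between groups and its 95% confidence interval.
- State that no claim of equality or of no difference follows from p>0.05.
- For any such claim, state a margin in advance and require the confidence interval to exclude it.
- Label the comparison of chosen with randomised Healthdot as descriptive.

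The cost is a wording change, and the sponsor gives up claims of no difference on these endpoints. Estimation needs no extra patients. A margin-based claim might. As an illustration only, borrow the 7-point margin at one-sided 0.05 and assume equal true rates: 80% power needs n = (1.645 + 0.8416)² × 2p(1 − p)/0.07², which is 120, 228, 404 and 530 per group at event rates p of 5%, 10%, 20% and 30%. At 100 per group the power is 73%, 50%, 34% and 29%. In exchange, if outpatients are truly 10 points worse, the chance of a wrongly favourable conclusion falls from 32% to 1% at a 5% control rate, and from 48% to 1% at a 10% control rate (against the two-sided test).

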### Secondary objective(s)

- To assess Patient satisfaction (on a scale of 1-10) in both groups
- To assess feasibility of outpatient recovery after standard bariatric surgery by evaluating recruitment rate, adherence to protocol and randomization, and the amount of missing data.

|                                                                                                                    |              |                        |                  |                    |
|--------------------------------------------------------------------------------------------------------------------|--------------|------------------------|------------------|--------------------|
| Title: Clinical Investigation Plan                                                                                 |              | Author: [name] |                  | Philips restricted |
| DocID: ICBE-2-36455                                                                                                | Version: 3.0 | Date: 2020-DEC-08      | Status: Approved | Page: 20 of 44     |
| This document is based on Philips Research Template: Clinical Investigation Plan, ID: QR-TEM-57, Date: 2019-Mar-21 |              |                        |                  |                    |

- To evaluate the percentage and total number of false-positive notifications from the Healthdot system.
- To evaluate the percentage of missed events (i.e. false negatives) from the Healthdot system.
- To evaluate the total number of missed minor events from the Healthdot system.
- To evaluate the outcome of patients who choose HD versus patients who were randomized to HD on a combined outcome measure as defined for the primary endpoint.
- To compare the number of adverse events in both groups
- To compare the use of pain medication during day of surgery until evening in both groups.
- To compare the clinical decisions made on basis of remote monitoring with the Healthdot system, to decisions which also include information from a telephone consultation
- To evaluate the impact of outpatient recovery after standard bariatric surgery and the Healthdot on patient and health professional satisfaction
- To evaluate the costs involved with outpatient recovery after standard bariatric surgery supported by Healthdot.
- To evaluate usability of the visualization of Healthdot data on the Guardian dashboard.

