- Percentage of false positive of the positive notifications from the Healthdot system
- Total number of false positive of the positive notifications from the Healthdot system
- Total number of false negative notifications from the Healthdot system
- The outcome of patients who choose HD versus patients who were randomized to HD on a combined outcome measure as defined for the primary endpoint.
- To evaluate the outcome of patients who choose HD versus patients who were randomized to HD on a combined outcome measure as defined for the primary endpoint.
- Number of adverse events in both groups
- Amount of pain medication taken on the day of surgery in both groups
- Percentage of clinical decisions made based on the Healthdot system, that changed when information from a telephone consultation was also included.
- Patient and health professional satisfaction (on a scale from 1-10) for both the outpatient recovery after standard bariatric surgery group as the current recovery path group
- The costs involved with outpatient recovery after standard bariatric surgery supported by Healthdot and the cost involved with the current recovery path, in the period up to 7 days after surgery.

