#### *Start of the study*

The activities in both groups are outlined in

[Table 1](#)

[Table 1](#), with the differences between the two groups described for clarity. Patients who have chosen to undergo outpatient recovery will be scheduled for surgery on the earliest available time-slots (before 12:00). The Healthdot will be applied mid-clavicular on the lowest left rib of the chest after surgery. HealthdotThe Healthdot can be removed by the patient themselves in case of emergency with a remover tissue which will be handed out to the patient before discharge. The patient will be instructed on how to remove the Healthdot with the tissue. The postoperative standard care will be arranged in such a way that same day discharge is possible for this group of patients. Patients who have chosen the regular recovery path will receive care in accordance with current protocol.

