| Day 1                                                                                                                                                                                                                                                                                                   |                                                                                                                                                                                                                                                                                                                |                                                                                                                                                    |
| Surgery, between 8:00h and 12:00h                                                                                                                                                                                                                                                                              | Surgery                                                                                                                                                                                                                                                                                                        | There is no difference in surgery since this is not part of the study. Surgery for patients leaving the same day is only scheduled in the morning. |
| By nurse, in the recovery room: 
 
- Application of the Healthdot device, if not already placed 5 days before surgery
 
                                                                                                                                           |                                                                                                                                                                                                                                                                                                                | Patients leaving hospital the same day receive the Healthdot device.                                                                               |

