| 
By nurse, under supervision of physician, around 20:00h:
 
 
- Anamnesis
 
- Physical examination
 
- Determine hemoglobin
 
 
This will be followed by discharge if criteria set by physician are met.
                                                                                                                                                           | 
By nurse, around 20:00h:
 
 
- Check EWS and pain score
 
- Inspecting the wound
 
- Ensure micturition within 6 hours after surgery
 
 
The patient will be observed during the night by the nurse.
                                                                                                                                                              | The outpatient group is evaluated for discharge. This will happen on day 2 for the regular treatment group. The procedures for both groups are the same and standard of care.                                                           |
| Day 2                                                                                                                                                                                                                                                                                                                                                                                                                            |                                                                                                                                                                                                                                                                                                                                                                                                                                         |                                                                                                                                                                                                                                         |

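### The pain-medication comparison ends at a clock time, but only outpatients are confined to morning surgery, so the postoperative hours counted can differ systematically between the groups

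*Protocol*

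**What the plan says.** The comparison is stated three times in the protocol. Section 5, Secondary objective(s): "To compare the use of pain medication during day of surgery until evening in both groups". Section 5, Secondary hypotheses: "The amount of pain medication during day of surgery until evening in both groups is not significantly different". Section 6.1, in the list of secondary endpoints: "Amount of pain medication taken on the day of surgery in both groups". The first two stop in the evening; the third runs for the day of surgery with no evening limit. None says when counting starts, and evening is not defined. The nearest clock time is in Table 1 (section 6.4), where the outpatient discharge assessment takes place "By nurse, under supervision of physician, around 20:00h".

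On timing of surgery, Table 1 gives the outpatient group "Surgery, between 8:00h and 12:00h". Its differences column adds: "Surgery for patients leaving the same day is only scheduled in the morning". The regular-group cell names surgery without a time, and section 6.4, Start of the study, says: "Patients who have chosen the regular recovery path will receive care in accordance with current protocol".

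Section 7 says that secondary endpoints will be tested with an uncorrected chi-squared statistic where that is appropriate. It mentions no adjustment for time since surgery. Section 5 says that the secondary hypotheses will be accepted or rejected on the trial's results, and that claims may be derived from them.

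**The concern.** The quantity compared is a raw amount. Its window has an end set by the clock and, in one group only, a restriction on when surgery takes place. If the average surgery time differs between groups, so does the number of postoperative hours in which medication can be given and counted. That difference follows the group and not the patient's pain.

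Two errors are possible. With identical hourly use, the group observed longer shows more medication, and the hypothesis of no difference may be rejected because of scheduling. Conversely, lower hourly use among outpatients may be offset by their longer window, so that the totals look alike. In neither case does the result describe analgesic need under the two recovery paths.

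The mismatch between sections 5 and 6.1 adds a second problem. If the window runs past the evening, its last hours fall at home for discharged outpatients and on the ward for regular patients. Doses would then be recorded under different conditions in the two groups.

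**Working it through.** The protocol gives no figure for this comparison, so there is none to reproduce. The sample size in section 7 concerns the primary endpoint and plays no part here.

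**Inputs from the protocol.** Outpatient surgery 8:00 to 12:00 (Table 1). Evening taken as about 20:00, the only related clock time (Table 1). 100 patients per group (section 7).

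**Assumptions, not in the protocol.** Regular-group surgery hours, varied below. Start times uniform within each range. Equal and constant hourly use in both groups. Counting starts at the surgery time, because no duration of surgery is given; an equal duration in both groups would leave the gap in hours unchanged.

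**Step 1: hours counted.** Mean window = 20 − mean surgery time. For outpatients: 20 − (8 + 12)/2 = 10 h, with individual windows from 20 − 12 = 8 h to 20 − 8 = 12 h.

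**Step 2: ratio of totals.** With equal hourly use, outpatient total / regular total = 10 / (mean regular window).

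| Regular surgery (assumed) | Mean regular window | Outpatient / regular |
|---|---|---|
| 8:00 to 12:00 | 20 − 10 = 10 h | 10/10 = 1.00 |
| 8:00 to 14:00 | 20 − 11 = 9 h | 10/9 = 1.11 |
| 8:00 to 16:00 | 20 − 12 = 8 h | 10/8 = 1.25 |
| 8:00 to 17:00 | 20 − 12.5 = 7.5 h | 10/7.5 = 1.33 |
| 12:00 to 16:00 | 20 − 14 = 6 h | 10/6 = 1.67 |

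**Step 3: chance of a spurious difference.** A simulation used 100 patients per group, the start times above and the same true hourly use in both groups. Between-patient coefficients of variation ran from 1.0 down to 0.4 (assumed, gamma-distributed). Each of 4,000 runs per setting was tested with a Welch t test at two-sided 0.05. The share of runs declaring a difference was:

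- regular surgery 8:00 to 12:00: 4.5 to 5.0%
- 8:00 to 14:00: 11.6 to 39.9%
- 8:00 to 16:00: 32.5 to 93.0%
- 8:00 to 17:00: 48.8 to 98.6%
- 12:00 to 16:00: 93.2 to 100%

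Except in the first line, where the windows match, the lower figure belongs to the coefficient of 1.0 and the higher to 0.4. The t test is a choice made for the check; the protocol does not name a test for an amount.

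**Step 4: masking.** If regular surgery ran 8:00 to 16:00 and outpatients used 0.8 times the regular hourly amount, the totals would be 0.8 × 10 = 8 and 1 × 8 = 8. A 20% lower hourly use would be invisible.

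**Step 5: the section 6.1 wording.** Extending the window to midnight adds 4 h to each group. The mean gap stays the same: for 8:00 to 16:00, 14 − 12 = 2 h, as in 10 − 8 = 2 h. The ratio falls to 14/12 = 1.17 but does not reach 1.

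**The case against.** The strongest objection is that the protocol never says when regular patients are operated on. It names no afternoon list. If both groups had surgery in the same hours, the problem would vanish. This stands: unequal average start times are an inference from a restriction on one group and from outpatients being given the earliest slots. It limits what can be said about size, but nothing in the protocol requires matching hours.

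The assumption of constant hourly use is also open to challenge. Analgesic need may change with time since surgery, and any doses before or during surgery that count would not grow with postoperative hours and would dilute the ratio. This stands too, so direction and size are likely and not certain.

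A reader might infer a ratio as high as (20 − 8)/(20 − 16) = 3.0. That sets the earliest outpatient case against a late regular case under an assumed schedule. It is not a contrast between groups, and the protocol does not support it.

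A reader might also infer that, under the section 6.1 wording, evening doses would count for outpatients only. They would not: the endpoint covers both groups, and regular patients' ward doses that evening count as well. What differs is where doses are taken and recorded, not the length of the window.

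It can fairly be said that the evening limit in section 5 already keeps the window roughly within the hospital stay of both groups, and that section 7 leaves the choice of secondary methods open. The first point deals with home recording but not with unequal hours. The second does not remove the defect, because the window is part of the endpoint as the protocol states it.

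**Conclusion.** The concern holds in a limited form. As written, the protocol compares raw amounts over windows that end at the same time of day while the timing of surgery is restricted in one group only, and it provides no correction for the resulting hours. Whether this biases the comparison, and by how much, depends on regular-group surgery times that the document does not give. Under the stated assumptions the outpatient total is 1.0 times the regular total if the hours match, about 1.1 to 1.3 times if regular surgery extends into the afternoon, and 1.67 times if all of it falls between 12:00 and 16:00. More counted medication among outpatients is the likelier direction but is not assured.

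Separately, sections 5 and 6.1 state different ends to the window and must be reconciled.

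One secondary endpoint is affected. The primary endpoint, the sample size and the criterion for trial success are untouched. The point still merits correction because section 5 commits to a decision on this hypothesis and permits claims from it.

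**What to change.** Define one window in the objective and hypothesis of section 5 and in the endpoint list of section 6.1: the same fixed number of hours from the end of surgery in both groups, lying within the period when both groups are in hospital. Alternatives are to analyse the amount per postoperative hour observed, or to adjust for surgery end time. Any of these needs surgery end time and administration times to be captured.

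The cost is a change of wording and a small amount of extra data extraction; the protocol does not say whether these times are already collected. A common window also leaves out doses given beyond it, so the endpoint would describe early in-hospital use only. Neither patient care nor the sample size changes.
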